#### Protected health information

2.5.4

This study will include access to participants' medical records to obtain medical background information, therapy information, and registry-related outcome measures collected as part of usual care. Therefore, HIPAA (Health Insurance Portability and Accountability Act) language will be included in the consent form.

### Data analysis

2.6

All registry data will be summarized with descriptive statistics (mean, median, range, and SD) for continuous data and counts and percentages for categorical data at each scheduled timepoint assessment. No minimum number of therapy sessions or device usage is required for inclusion in descriptive analyses. Established minimal clinically important difference (MCID) thresholds for motor and patient-reported outcomes will be used to aid interpretation, where applicable. The approach to handling missing data will be determined based on the type and extent of the missing data, with specific models to be defined prior to formal data analysis.

IPG usage data are downloaded at the completion of in-clinic therapy and at each subsequent in-clinic follow-up visit through 3 years. Study forms instruct sites to download IPG data at each applicable post-therapy visit. If a scheduled download is missed, data remain stored on the device and may be retrieved at a subsequent visit. Missing or unavailable device data will be documented and summarized descriptively.

Additional exploratory analyses to supplement the results or for research may be performed, as appropriate.

### Changes to methods

2.7

The exclusion criteria were modified from a previous protocol version to allow retrospective enrollment for patients who consent after implantation. There are no timeline restrictions. This change was made to maximize data capture in the registry, as some sites were performing commercial implants prior to formally participating as study sites.

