#### Inclusion and exclusion criteria

2.2.1

To be enrolled in the registry, participants must meet the following inclusion criteria:

Have a history of stroke with moderate-to-severe upper limb deficits and be clinically judged to be a good candidate for Paired VNS Therapy.Intend to be implanted with the Vivistim System (whether or not they actually do get implanted).Be aged 18 years or older.

Individuals will be excluded if they:

Have not had a stroke.Do not have upper limb deficits.Are currently enrolled in an investigational study.

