#### Data collection timeline

2.4.1

Registry data will be collected for up to 3 years, as outlined in Table 1 (additional study forms are included in the Supplementary Data Sheet 1). All participants will contribute baseline information including demographics, medical history, motor assessments, patient-reported outcome measures, and healthcare utilization. For participants who receive the device, baseline data will be collected before the initiation of therapy, which could be prior to implantation and up to and including the day stimulation is activated after implantation. Follow-up data will be collected at 3 and 6 months after Paired VNS is first initiated, and annually for 3 years thereafter. Surgical details such as device serial number and procedure date will be collected for participants who undergo implantation of the Paired VNS System. Persons who enroll but are not implanted may continue to be followed up at the same time points based on their date of registry entry.

**Table 1 T1:** Data collection timeline^*^.

Assessments	Enroll	Baseline	Post implant	End of therapy	3 month	6 month	1 year	2 year	3 year
General documentation									
Consent	X								
Demographics		X							
Baseline rehabilitation assessment		X							
Surgery details			X						
Motor outcome assessments									
FMA-UE		X			X	X	X	X	X
WMFT (optional)		X			X	X	X	X	X
9 HP		X			X	X	X	X	X
Patient-reported outcomes									
Quality of life		X			X	X	X	X	X
SIS		X			X	X	X	X	X
MAL		X			X	X	X	X	X
BDI		X			X	X	X	X	X
Global impression of change					X	X	X	X	X
Other forms									
Healthcare utilization		X					X	X	X
Rehabilitation assessment					X	X	X	X	X
Therapy information				X	X	X	X	X	X
Participant satisfaction survey					X	X	X	X	X
Therapist satisfaction survey					X	X	X	X	X
Satisfaction survey					X	X	X	X	X

9 HP, Nine Hole Peg Test; BDI, Beck Depression Inventory; FMA-UE, Fugl-Meyer Assessment–Upper Extremity; MAL, Motor Activity Log; SIS, Stroke Impact Scale; WMFT, Wolf Motor Function Test.

^*^Demographic information and baseline measures are performed within 30 days of surgery. Three- and 6-month assessments and questionnaires are collected ±15 days of the target date. 1-, 2-, and 3-year assessments and questionnaires are collected ±60 days of the target date.

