#### Provisions to protect the privacy interests of participants

2.5.3

On-site data collection for the registry should occur in a private clinical space without interference from other staff or patients. Participants can choose whether to transmit survey questionnaires via email or whether to complete them in person during in-clinic visits. Participants will be made aware that some information for the registry will be collected from their therapist and surgeon or surgeon's staff and recorded under a unique study identifier to protect their privacy. As necessary for collecting such information, the participant will be asked to sign a standard release of information form. Some health-related data or measures collected as part of usual care may be obtained directly from the participant's electronic medical record. Participants may ask questions at any time throughout their registry participation, including information about scores on outcome measures collected.

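### Open-ended consent after implantation, with no separation in the summaries, is liable to over-represent patients who did well and stayed in contact

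*Protocol article*

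**What the plan says.** Section 2.7 (Changes to methods) describes the rule now in force. The exclusion criteria were changed "to allow retrospective enrollment for patients who consent after implantation. There are no timeline restrictions". The reason given is operational: "This change was made to maximize data capture in the registry, as some sites were performing commercial implants prior to formally participating as study sites".

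Three other sections bear on this:

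- Section 2.2.1 still requires participants to "Intend to be implanted with the Vivistim System (whether or not they actually do get implanted"), which is wording for someone not yet implanted.
- Section 2.4.1 states that "All participants will contribute baseline information including demographics, medical history, motor assessments, patient-reported outcome measures, and healthcare utilization". For implanted participants this baseline must precede the start of therapy, with the day of activation as the last permitted day.
- Section 2.6 states that "All registry data will be summarized with descriptive statistics (mean, median, range, and SD) for continuous data", at each scheduled timepoint, with MCID thresholds as an aid to interpretation. It adds that "No minimum number of therapy sessions or device usage is required for inclusion in descriptive analyses".

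Section 2.5.3 opens a route for data that predate consent: "Some health-related data or measures collected as part of usual care may be obtained directly from the participant's electronic medical record". The Limitations (section 4.1) mention selection bias only in connection with open-label delivery. The optional strata named there are baseline characteristics, therapy exposure and site-level factors. Timing of consent is not among them.

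**The concern.** A person who consents before the first Paired VNS session enters the registry with the outcome unknown. A person who consents months or years later may enter with it known, both to the person and to the site that decides whom to approach. Two kinds of selection can follow. One is on survival and contact: a patient who died or was lost before being asked cannot be enrolled. The other is on response: a patient who is pleased with the result may be likelier to be asked and to agree.

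The registry's outputs are means, percentages and readings against MCID thresholds at each visit. Selection acts directly on these, so a descriptive purpose does not protect them. Durability is the most exposed, because the longest follow-up available at any date comes from the earliest implants, and those include the ones done before sites had joined.

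**Working it through.** The article states no sample size, effect, SD or number of late consenters, so there is no figure of its own to reproduce. Three checks were made.

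**1. The sections side by side.** Section 2.7 admits people already implanted. Section 2.2.1 admits people who intend to be. Section 2.7 says that the exclusion criteria were modified and mentions no change to the inclusion criteria, so the two do not fit together. Section 2.4.1 requires a pre-therapy baseline from everyone. A person who consents after therapy began can supply one only from earlier records, and the article does not say how that applies to this group. No section splits the summaries by timing of consent or sets a latest point for it.

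**2. Dates (all from the article).**

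- Commercial distribution began in May 2022, the first site was activated in December 2022 and the first participant enrolled in April 2023. The gaps from May 2022 are 7 and 11 months.
- May 2022 to the status date of January 2026 is 44 months. The last visit is at 36 months, or about 38 with the 60-day window. Consent after every scheduled visit has passed is therefore possible for the earliest implants, unless therapy started more than about 6 months after surgery (44 − 38 = 6).
- Earliest prospective 3-year visit: enrolment on 1 April 2023 with therapy starting that day, plus 3 years, is 1 April 2026. Subtracting the 60-day window gives 31 January 2026. Any later enrolment or therapy start moves this date later. So 3-year data held before 31 January 2026 could come only from people who consented after first Paired VNS.

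**3. Size, on assumed inputs only.** Let p be the true responder rate, f the share of participants who consent after their outcome is known, and RR how many times likelier responders are than non-responders to be enrolled late. Prospective entrants are taken to show the true rate.

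- Rate among late consenters: r = p·RR / (p·RR + 1 − p)
- Pooled rate: (1 − f)·p + f·r
- Bias: f·(r − p)

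With p = 0.50 and RR = 2, r = 1.00/1.50 = 0.667.

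| f | pooled rate | bias (points) |
|---|---|---|
| 0.10 | 0.517 | +1.7 |
| 0.25 | 0.542 | +4.2 |
| 0.50 | 0.583 | +8.3 |

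Over p from 0.4 to 0.6, RR from 1.5 to 3 and f from 0.10 to 0.50, the extremes are:

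- lowest (p = 0.6, RR = 1.5, f = 0.10): r = 0.9/1.3 = 0.692, bias 0.10 × 0.092 = +0.9 points
- highest (p = 0.4, RR = 3, f = 0.50): r = 1.2/1.8 = 0.667, bias 0.50 × 0.267 = +13.3 points

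At RR = 1, r = p and the bias is 0. Below 1 it changes sign.

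A second illustration uses FMA-UE change, also wholly assumed: true change normal with mean 4 and SD 5, 40% consenting, and odds of consent multiplied by 1.05, 1.1 or 1.2 per point gained. Simulated means among late consenters are 4.73, 5.4 and 6.33. The pooled mean is 4 + f × (late mean − 4). It runs from 4 + 0.25 × 0.73 = 4.18 to 4 + 0.50 × 2.33 = 5.17 for f between 0.25 and 0.50.

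If the main set contains only people who consented on or before first Paired VNS, f = 0 and this source of bias is 0 whatever p and RR are.

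**The case against.** The strongest reply is that this is a disclosed choice, made for a reason unrelated to outcome, in a descriptive registry that disclaims causal inference. The full protocol or an analysis plan may define analysis sets, and the optional stratification and exploratory analyses leave room to split by consent timing. This has weight: a flag built from dates could still be derived at analysis. But the stated reason explains who became eligible, not who is later approached and agrees. The article also fixes an unlimited entry rule beside inclusion and baseline text that does not fit it.

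Several stronger readings are tempting, and the documents do not support them:

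- *Results will certainly be inflated.* The upward direction is expected, but no figure in the article shows it.
- *Explanted, non-using or disappointed patients can never appear.* They remain eligible, and section 2.6 sets no minimum use. At most they may be less likely to consent. Only those who died or were lost before consent are excluded outright.
- *No one who consents after implantation can have a valid baseline.* A person who consents between implantation and activation can give one prospectively, with no response yet known.
- *Baselines may be recalled.* Nothing permits this. Section 2.4.1 requires collection before therapy, and a late consenter with no recorded baseline has missing data and cannot contribute to change from baseline. That limits the effect on change scores.
- *This is immortal time bias.* No time-to-event analysis is planned and there is currently no non-implant group. Selection on survival and contact is the accurate description.
- *Biased 3-year results already exist.* The article reports no outcomes and does not say that any 3-year data are held.

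**Conclusion.** The point holds as a liability to bias, not as a demonstrated bias. Followed as written, the plan mixes people who may have entered knowing their outcome with people who could not have known it, and its Limitations do not name this route. Selection on survival and contact follows almost directly from the entry rule. Selection on good response is plausible but unproven.

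The size cannot be computed, because the article gives over 200 enrolled and 150 implanted but not how many consented after therapy began. The ranges shown rest entirely on assumed inputs and include zero if consent is unrelated to outcome. The firm figures are those from the dates: 44 months of possible lag at most, which is a ceiling for a first-month implant, and 31 January 2026 as the earliest date for a prospectively consented 3-year assessment.

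**What to change.** 1. Flag each participant by consent date relative to first Paired VNS. Consent between implantation and activation counts as prospective. State the number in each group.
2. Make those who consented on or before first Paired VNS the main set for change, MCID and durability results.
3. Report later consenters separately. Mark visits that predate their consent, and use only dated baselines recorded before stimulation, as section 2.4.1 already requires.
4. Reconcile the inclusion criterion in section 2.2.1 and the baseline statement in section 2.4.1 with section 2.7.
5. Name this selection route in section 4.1.

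Retrospective enrolment can continue and no data are discarded. The work is one derived variable, some wording and extra table columns. The price is a smaller main set and later 3-year results.

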## Results

3

### Current status

3.1

The first GRASP registry site was activated in December 2022, and the first participant enrolled in April 2023. Active registry sites encompass a broad range of care settings, including academic medical centers, community hospitals, outpatient rehabilitation clinics, private practices, and mobile therapy providers. As of January 2026, there are over 60 active sites across 39 states with over 200 participants enrolled and 150 implanted with the Vivistim Paired VNS System. A non-implant group is not currently available, as all enrolled participants have either received the device or are awaiting implantation. Enrollment remains ongoing.

Future publications reporting on registry outcomes will be led by principal investigators or participating site clinicians comprising the GRASP Registry authorship group to minimize potential bias. Lead authors will have access to registry data and will assume primary responsibility for data interpretation, manuscript preparation, and submission.

## Discussion

4

Upper limb paresis is one of the most common and persistent consequences of stroke, with up to 65% of people unable to fully incorporate their affected limb into daily activities by 6 months post-stroke (Dobkin, 2005). These enduring upper limb deficits are a leading contributor to long-term disability, diminishing a person's quality of life and limiting participation in meaningful activities (Lieshout et al., 2020). The Vivistim Paired VNS System is an approved treatment for chronic stroke upper limb recovery that has been shown to reduce motor deficits, improve functional outcomes, and enhance engagement and quality of life (Dawson et al., 2021; Kimberley et al., 2025). The GRASP registry extends this evidence by systematically collecting real-world outcomes from individuals receiving VNS paired with rehabilitation therapy. These data will enable a deeper understanding of patient characteristics and experiences, therapy delivery, and clinical practice.

### Limitations

4.1

The observational design of this registry precludes causal inference, and the open-label delivery of commercially available Paired VNS Therapy may introduce selection or expectation biases. To address these limitations, analyses will primarily be descriptive, emphasizing characterization of real-world outcomes, practice patterns, and variability in therapy utilization. Where feasible, outcomes may be explored and stratified by baseline characteristics, therapy exposure, or site-level factors to better contextualize findings.

Variability in clinical practice across sites may make direct comparisons and interpretation of outcomes more challenging. However, this heterogeneity is an inherent and valuable feature of real-world evidence. By capturing data across diverse clinical environments, the registry enables evaluation of differences in care delivery, resources, and outcomes in routine practice. This approach complements rigorously controlled clinical trial data by providing insight into real-world implementation and utilization.

The extended duration of follow-up may increase the likelihood of participant attrition and missing data. While participant retention strategies are employed, missing data will be evaluated based on the extent and pattern of missingness and addressed using appropriate analytic approaches, with results interpreted accordingly by principal investigators.

The Vivistim System is currently approved and commercially available in the U.S. only. As such, the GRASP registry is designed to collect real-world evidence relevant to U.S. clinical practice, and findings are therefore most directly applicable to healthcare systems with similar access to surgical implantation and rehabilitation infrastructure.

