#### Good clinical practices and role of the sponsor

2.3.5

The WCG Institutional Review Board approved the study protocol on February 21, 2022, under tracking identifier 20220693, and the study will be conducted in accordance with the principles outlined in the Declaration of Helsinki. All participants will provide written informed consent prior to participating in the study.

The study sponsor developed this protocol and is responsible for overseeing data collection, management, and analysis. The sponsor has no role in clinical decision-making, outcome assessment, or delivery of rehabilitation therapy. Study investigators include independent clinicians who are directly responsible for patient enrollment and data collection. Publications reporting study outcomes will be led by principal investigators from participating sites. Lead authors will have full access to the study data and will assume primary responsibility for data interpretation, manuscript preparation, and submission.

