A physical or occupational therapist will perform baseline rehabilitation assessments and subsequent follow-up therapy evaluations. The assessments will document hand dominance, side of paresis, range of motion, strength, gross motor function, fine motor control, spasticity, sensory function, pain, and activity limitations. Appropriate rehabilitation goals and individual patient goals will also be included.

After completing all in-clinic therapy sessions, additional therapy-related information will be collected, including the total number of in-clinic sessions, the frequency of self-activated sessions, and downloaded IPG data.

Because this registry is observational and does not mandate therapy delivery or assessment adjudication at different sites, no formal primary or secondary outcome hierarchy was prespecified.

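### Section 4.1 presents descriptive analysis as the answer to selection and expectation bias; it limits the inference but removes neither bias

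*Protocol article*

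**What the plan says.** Section 4.1 (Limitations) first states that the observational design rules out causal inference, then that "the open-label delivery of commercially available Paired VNS Therapy may introduce selection or expectation biases". The next sentence gives the response: "To address these limitations, analyses will primarily be descriptive, emphasizing characterization of real-world outcomes, practice patterns, and variability in therapy utilization". A second, optional measure follows: "Where feasible, outcomes may be explored and stratified by baseline characteristics, therapy exposure, or site-level factors to better contextualize findings".

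Other sections bear on how these biases could enter:

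- **Score access (2.5.3).** "Participants may ask questions at any time throughout their registry participation, including information about scores on outcome measures collected". The article sets no order between learning a score and completing that visit's self-reports.
- **Entry (1.2, 2.7).** Participation is voluntary. Enrolment after implantation is allowed with no time limit, because "some sites were performing commercial implants prior to formally participating as study sites".
- **Counts (3.1).** As of January 2026 there were over 200 enrolled and 150 implanted, all of them registry participants. No non-implant group is available at present.
- **Assessment (2.4.1, 2.3.5).** The registry "does not mandate therapy delivery or assessment adjudication at different sites". The separation that is stated concerns the sponsor: "The sponsor has no role in clinical decision-making, outcome assessment, or delivery of rehabilitation therapy".
- **Use of the results (2.6, 5).** Outcomes will be read against MCID thresholds. The conclusion promises insight into how the therapy affects arm and hand function, and support for generalizability.

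**The concern.** The stated remedy does not act on the stated problem. Describing a result rather than testing it limits what may be claimed, but the number itself is unchanged. If expectation lifts follow-up ratings, or if patients who do well are more likely to enter, the descriptive mean and the proportion reaching an MCID include that lift. With no comparator group at present, nothing in the data would show it.

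A reader of 4.1 could therefore take the two biases as dealt with, and then meet effect wording and a generalizability claim in section 5. The registry would yield no figure from which to judge how large either bias might be.

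**Working it through.** The article states no sample size, power, SD or target effect, so there is no design figure to reproduce. The check is to ask what descriptive analysis does to each bias.

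**1. Expectation or rater shift.** Let the true scores be Y0 at baseline and Y1 at follow-up, with rating shifts b0 and b1.

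Observed change = (Y1 + b1) − (Y0 + b0) = true change + (b1 − b0).

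A constant leniency cancels. A shift that differs between baseline and follow-up passes one-for-one into the mean change, and also moves the share reaching an MCID. Descriptive reporting leaves b1 − b0 untouched.

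For scale only: section 2.4.2.1 gives the FMA-UE 33 items and a maximum of 66, scored 0, 1 or 2 except for reflex activity (0 or 2). One level of extra generosity at follow-up on an assumed 3 to 5 non-reflex items is 3 to 5 points, or 3/66 = 4.5% to 5/66 = 7.6% of the scale.

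**2. Selection.** Let f be the share of all implanted patients who are in the registry, E the mean change among them, and N the mean change among those not enrolled.

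Mean of all implanted = f·E + (1 − f)·N, so E − mean of all = (1 − f)(E − N).

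The article gives 150 registry implants and no total. With assumed totals:

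| Assumed total implants | f = 150/total | Factor (1 − f) |
|---|---|---|
| 150 | 1.00 | 0 |
| 300 | 0.50 | 0.50 |
| 600 | 0.25 | 0.75 |
| 1,500 | 0.10 | 0.90 |

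With an assumed difference of 0.5 SD and an assumed SD of 6 FMA-UE points, capture of 30% gives 0.70 × 0.5 = 0.35 SD (2.1 points), and capture of 70% gives 0.30 × 0.5 = 0.15 SD (0.9 points). Without the denominator, the factor could lie anywhere from 0 to near 1.

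**3. Stratification.** Sorting enrolled patients by baseline, exposure or site gives no information on N, which concerns people outside the data. Within each stratum b1 − b0 remains. The optional measure therefore removes neither bias.

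**4. Routes of entry, set side by side.**

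- Score questions are allowed at any time (2.5.3), and no order relative to the self-reports or the global impression is stated. Priming of self-reports by known scores is possible but not shown.
- Consent may follow implantation with no time limit (2.7). By its terms this allows entry after therapy has begun, when response may already be visible.
- Section 2.4.1 says "A physical or occupational therapist will perform baseline rehabilitation assessments and subsequent follow-up therapy evaluations". That sentence concerns rehabilitation assessments, which Table 1 lists in rows separate from the FMA-UE and WMFT. It does not say who scores the motor scales.

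**The case against.** The strongest reply is that this turns on one verb in a Limitations section. The limitations in question begin with the bar on causal inference, for which a descriptive aim is the right response; both biases are openly disclosed; and a second measure is offered. All of that is fair. There is no concealment, and the descriptive aim is not at fault. What stands is that the sentence also covers selection and expectation bias, which description leaves in place, and that section 5 then uses effect wording.

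Three stronger readings are tempting, and the article does not support them:

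- *Treating therapists score their own patients.* No section says so. The sentence on therapists covers other assessments, and the study forms (Supplementary Data Sheet 1) and monitoring plan are not shown. The article is silent on who rates, and a condensed article may leave that to the forms. It also reports excellent rater consistency for the FMA-UE, though consistency does not exclude a shared shift over time.
- *Participants learn scores before answering questionnaires.* Section 2.5.3 permits questions at any time but fixes no order, and emailed forms need not follow motor testing.
- *Implants before a site joined show poor capture.* Section 2.7 cites them as the reason for widening enrolment, which tends to raise coverage. It also admits late entry, so the net direction is unknown.

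Generalizability is already qualified in 4.1 to the U.S. and similar health systems. That qualification concerns setting, not which implanted patients enter.

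**Conclusion.** The point holds in limited form. Primarily descriptive analysis is a fair answer to the lack of causal inference, but not to selection or expectation bias, and optional stratification does not close the gap. The firm textual ground is the wording of 4.1 set against section 5, the open score access in 2.5.3, and voluntary entry with no time limit after implantation. The missing rater information is silence and carries less weight.

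No size can be derived from the article. The 3 to 5 FMA-UE points, the capture fractions, the 0.5 SD difference and the SD of 6 are all assumptions that show scale, and a rater shift matters only if it differs between baseline and follow-up. Nothing here invalidates the registry. The changes affect what it can credibly conclude, and because enrolment is ongoing they can still apply to future visits.

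**What to change.** 1. **Wording.** Say in 4.1 that descriptive reporting limits the inference but does not remove selection or expectation bias. In section 5, replace the effect wording with wording about observed change.
2. **Order.** At each visit, complete the self-reports and the patient global impression before motor testing, with emailed forms returned before the visit. Give scores only afterwards. Participants keep access; only the timing changes.
3. **Rater field.** On the FMA-UE, WMFT and clinician global-impression forms, record whether the rater has delivered Paired VNS to that participant, and report change by that status. A second therapist need not be required.
4. **Capture fraction.** Report registry participants implanted over all commercial implants in the same period, with numerator and denominator matched. Pre-activation implants eligible for retrospective enrolment belong in both; counting only implants since activation in the denominator could give a ratio above 1. At sites that deliver therapy but do not implant, use patients treated as the base. This depends on the sponsor's commercial records being available, which is an assumption.
5. **Timing of consent.** Report results separately for participants who consented before and after therapy started.

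The cost is a form field, an ordering instruction with some scheduling work for emailed forms, one count from records, and revised text. Measures already taken from usual-care records may lack the rater field and should be reported as unknown. Results may look less favourable.
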